#### Primary outcomes

The primary outcome is the proportion of documented cases of offending within 20 months of randomization, based on police records supplemented by information obtained from the young person, parents/caregivers and social care services. While this may be only a partial or even an inaccurate reflection of the psychological conditions and social behaviours of the participants, it is the indicator of primary concern for the funders of the programme as, in most cases, this record triggers costly juvenile justice and social interventions. A linked outcome, of similarly high concern to funders of services, is assignment to long-term (3 months or longer) out-of-home placements in specialist residential provision when social services consider that the safety of the participant’s family or community is compromised by the individual, even in the absence of arrest and conviction. This means all participants who are placed into local authority care, are incarcerated, long-term hospitalized or offered residential schooling at any time in the 20 months following randomization will not be considered to have moved from the offending to the non-offending group. This information will be obtained from caregivers and cross-referenced with documented information from the national social care services database to maximize accuracy. The investigators expect this trial to give information on how many young people assigned to MAU and to MST-PSB require specialist residential provision either immediately after intervention or during the follow-up period.

#### Secondary outcomes

Secondary outcomes are limited in number to reduce the measurement burden on young people and their primary carer(s), as the investigators’ previous experience has shown that having too many measures to complete is a disincentive to continued participation [25, 28]. The domains that the investigators consider key to the intervention, and consistent with previous RCTs of MST-PSB, are youth sexual and non-sexual offending, adolescent well-being and family functioning. Although rarely measured to date, we will also assess deviant sexual interests, given their specific association with adolescent sexual offending found in a recent meta-analysis seeking to understand what differentiates adolescent sexual offenders from general antisocial offenders [10]. Economic data that are highly relevant to conducting a comprehensive cost-benefit analysis will be collected alongside these outcomes. The study will also collect data on variables associated with key mechanisms of change that are documented in the literature on standard MST [49] and confirmed in trials of sexual offenders [46]: parent-adolescent relationships and young people’s associations with deviant peers. Furthermore, the study will evaluate parenting skills in detail, given that the MST model aims to improve outcomes for young people by targeting caregivers as being primarily responsible for facilitating change. Adolescent symptoms have been shown to decrease with increased supportiveness and decreased conflict between parents [51, 52], and decreases in youth antisocial behaviour, deviant sexual interests and sexual risk behaviours have been associated with caregivers’ ability to follow through with disciplinary practices and having decreased concern about their adolescents continuing to associate with antisocial peers [46]. Furthermore, adherence to the MST manual by therapists appears to improve treatment outcomes: treatment fidelity leads to better family functioning, which in turn decreases deviant peer affiliation, leading to decreased delinquent behaviour [49].

#### Objective measures

Objective outcomes will be collected from reports of sexual and non-sexual offending behaviour based on police computer records, including details of custodial sentences. These measures will be taken at 6-month intervals, for the 6 months before randomization, the 8 months covering the intervention period (adjusted as MST-PSB lasts on average 5 to 7 months), and 6-monthly until the 20-month follow-up point. The number of records of offending behaviour (count data) will be obtained and 6-month periods free of any offending behaviour will also be recorded (binary data). Records will be obtained from the Police National Computer as well as from the Young Offender Information System database; these records detail information on offences, court appearances, criminal orders, police custody records and arrest rates. Records of school attendance and exclusions will be retrieved from both the schools themselves and the National Pupil Database to assess educational outcomes.

#### Self-report

The RA will administer pre-testing questionnaires during the initial contact with the young person and family after they have consented and before group assignment. Post-testing by the RA will take place 8 months after entry into the study; it is intended that this will be a minimum of 2 weeks after the family completes the intervention (MST-PSB or MAU). Follow-up assessments will be made at 14 and 20 months post-randomization. Self-report measures of well-being and adjustment, antisocial behaviour, inappropriate sexual interests and difficulties, parenting skills and family functioning, as well as parental mental health and adjustment, will be collected.

#### Well-being and adjustment

A general assessment of well-being will be obtained using the Strengths and Difficulties Questionnaire [53]. Depression will be monitored using the Short Mood and Feelings self-report questionnaire [54], completed by the adolescents. Educational outcomes will include evaluation of participants’ emotional and behavioural functioning in the classroom using the Conners’ Comprehensive Behaviour Rating Scale [55].

#### Sexual adjustment and difficulties

The Multidimensional Inventory of Development, Sex, and Aggression (MIDSA) [56] and the Adolescent Sexual Behaviour Inventory (ASBI) (parent and youth forms) [57] will be used to assess the young person’s sexual adjustment, with a focus on inappropriate sexual interests and difficulties, as well as any prior history of maltreatment.

#### Antisocial behaviour

The prevalence and incidence of delinquent behaviour (for example, vandalism, theft, or burglary) and of peer delinquency will be assessed using the Self-Report Delinquency measure [58]. Non-compliance and increasingly serious forms of antisocial behaviour, as well as young people’s perceptions of law-abiding behaviour and institutions, will be assessed using the Antisocial Beliefs and Attitudes Scale [59]. Callous and unemotional traits will be assessed using the Inventory of Callous-Unemotional Traits, an updated version of the Antisocial Process Screening Device [60]. The investigators predict that MST-PSB will achieve decreases in adolescents’ associations with antisocial peers, increases in positive peer relations and greater commitment to prosocial activities. This prediction is consistent with the MST model and hypothesized mediating mechanisms [46] and is relevant to social policy initiatives and concerns.

#### Parenting skills and family functioning

The quality of the relationship between adolescent and carer(s), family functioning and parenting practices will be assessed using the Family Adaptability and Cohesion Scales [61], the Inventory of Parent and Peer Attachment-Revised [62] and Loeber et al.'s parent-completed measure of positive parenting and disciplinary practices, along with parental monitoring and supervision [63] . Parental disruption and conflicts will be assessed using the short form of the Conflict Tactics Scale [64].

#### Parental mental health and adjustment

Parental mental health will be briefly assessed using the General Health Questionnaire-28 [65], a commonly used screening instrument.

### Interviews

#### Demographics interview

A bespoke interview (Demographic Interview for Parents) covering general family information, including parental forensic history, schooling and economic information, constructed by the investigators, will be administered to all parents.

#### Interviews involving young people

Child psychometrics will be obtained by using the Wechsler Abbreviated Scale of Intelligence [66]. Psychiatric disorders will be identified and a psychosis screen provided by the Development and Well-Being Assessment [67], a computerized structured interview measure that will be administered to the carers and young people. The quality of the parent-adolescent attachment relationship will be assessed with the Child Attachment Interview [68].

#### Experience of MST

After the intervention, young people and their carer(s) will be interviewed to elicit their views regarding their experience of MST and factors that they perceive had facilitated or inhibited therapeutic change, based on qualitative research carried out during the Brandon Centre trial [69] and the more recent START trial [28].

### Health economic evaluation

Health economic analysis will be conducted by the Centre for the Economics of Mental Health at the Institute of Psychiatry, London. This analysis will explore the relative costs and cost-effectiveness of MST-PSB and MAU. The evaluation will take a broad perspective and will include all health, social services, education and voluntary sector services, as well as costs to the criminal justice sector, costs resulting from crimes committed, and out-of-pocket expenses to the young people and their families.

Data on MST contacts will be collected directly from the Brandon Centre to avoid participants revealing their group allocation to the RAs. Data on the use of all other services will be collected in interviews using the Child and Adolescent Service Use Schedule (CA-SUS) and EQ-5D questionnaire, which have previously been used with young people with complex mental health and social care needs [70–73]. The CA-SUS will be adapted to the current study population by review of the literature and pilot testing, to ensure comprehensive coverage and face validity. The cost of the MST-PSB and MAU interventions will be calculated through a detailed micro-costing (or bottom-up) approach using standard costing methodology [74, 75]. This will involve estimation of the indirect time spent on individual cases, including preparation, meetings, telephone calls and supervision, as well as detailed recording of direct face-to-face contact.

### Programme components of Multisystemic Therapy for Youth with Problem Sexual Behaviours and management as usual

A bespoke fidelity measure, the Children and Young People - Resources, Evaluation and Systems Schedule (CYPRESS) ([name], [name], [name], [name], personal communication), will be used to enable accurate characterization of the programme components of MST-PSB and MAU interventions. This approach is based on the initiative of the MST developers [50], who undertook a large-scale transportability study of standard MST involving families, therapists, supervisors and consultants. Organizational structure and climate as rated by the therapists, supervisors and consultants appeared to predict the outcome of MST [76]. CYPRESS has been designed to characterize care pathways for antisocial youths in the UK context. The measure will be administered in an interview format to service managers and therapists, to elicit care-pathway-relevant information in three main domains: ethos and service characteristics (for example, service has a comprehensive and shared view of the model of care provided; service has explicit criteria describing the population served); team operations (for example, service has a comprehensive model of supervision that provides for all team members); and range of interventions available to young people and their families (for example, a range of individual, group or family interventions are provided by the team, which are consistent with the model of care). The use of CYPRESS will allow key programme elements associated with outcome to be identified. The use of a common measure will allow a comparison between MST-PSB and MAU in the three domains described above and potentially provide information on common aspects of service function associated with outcome. This type of approach has been used to characterize other complex interventions in mental health [77]. It will be of particular value in assessing the key beneficial organizational components of such a complex intervention as MST-PSB when it is deployed in a healthcare system radically different from that in which it was developed.

### Qualitative interviews

To obtain additional information about participants’ experience of MST-PSB and being in an RCT of this treatment, the semi-structured interview developed by Tighe and colleagues [69] in the Brandon Centre trial will be adapted for young people showing problem sexual behaviour. This 45-minute interview will elicit carers’ and young people’s experience of having participated in an RCT for problem sexual behaviour (that is, their experiences of discussing their harmful sexual behaviour as part of the initial visits prior to consent, completing the measures, and treatment allocation), their experiences of having received MST-PSB or MAU services, and their views of the costs and the benefits. Semi-structured interviews will be conducted to explore how young people and their parents or carers experienced MST-PSB or MAU, whether they think that the young person’s functioning or carers’ lives have changed following MST-PSB (in areas targeted by the intervention) or MAU, and whether family relationships have changed. If the young person or carer reports changes, the interview will also explore the timing of those changes and how MST-PSB or MAU affected the changes. Interviews will be audio recorded and transcribed verbatim. The interviews may broach sensitive and stigmatizing issues with young people and their carers pertaining to their having received treatment for sexually abusive behaviour. To the investigators’ knowledge, young sexual offenders are rarely provided with the opportunity to reflect on their difficulties, treatment and social attitudes toward their behaviour. Thus, the interviews may provide valuable insights that will inform treatment delivery.

Transcripts will be analysed thematically using Interpretative Phenomenological Analysis (IPA). The primary objective of IPA research is to understand how individuals make sense of their experiences [78]. The intention is for the interview to be administered to approximately 12 to 14 % of families per treatment condition by an interviewer who is independent of the intervention but not blind to treatment allocation. Specifically, doctoral students who are trained and supervised by experienced qualitative researchers will conduct the interviews. The qualitative interviewers are separate from the MST-PSB service providers and the RAs. A random sample of the audio-taped interviews will be re-rated by independent raters to examine the reliability of qualitative coding.

### Follow-up assessment

Follow-up assessments will be conducted at 8, 14 and 20 months post-randomization. Table 1 shows a detailed outline of the planned measures at each follow-up point throughout the trial.

**Table 1 Tab1:** Measures and schedule of administration in the STEPS-B trial of multisystemic therapy for problem sexual behaviour

Measure (abbreviation)	Parent		Young person		Independent source	Domain	Study month			
	Questionnaire	Interview	Questionnaire	Interview			0	8	14	20
Demographics Interview for Parents (DIP)		✓				Background	✓			
Social Service Records and Interview (SSR)		✓		✓	✓	Out-of-home placements		✓	✓	✓
Police Computer Records Report (PCRR)					✓	Youth antisocial	✓	✓	✓	✓
Exclusions from the National Pupil Database (NPD)					✓	Youth education	✓	✓	✓	✓
Strengths and Difficulties Questionnaire (SDQ)	✓		✓			Youth mental health/well-being	✓	✓	✓	✓
Conners’ Comprehensive Behaviour Rating Scale (CBRS)	✓					Youth school functioning; hyperactivity/impulsivity	✓	✓	✓	✓
Inventory of Callous-Unemotional Traits (ICU)	✓		✓			Youth callous-unemotional traits	✓	✓	✓	✓
Child and Adolescent Psychiatric Assessment (DAWBA)		✓		✓		Youth mental health profile	✓		✓	
Self-Report Delinquency (SRD)			✓			Youth antisocial	✓	✓	✓	✓
Adolescent Sexual Behaviour Inventory (ASBI)	✓		✓			Youth sex-related behaviours	✓	✓	✓	✓
Short Moods and Feelings Questionnaire (MFQ)			✓			Youth depression	✓	✓	✓	✓
Wechsler Abbreviated Scale of Intelligence (WASI)				✓		Youth psychometrics	✓			
Antisocial Beliefs and Attitudes Scale (ABAS)			✓			Youth antisocial cognition	✓	✓	✓	✓
Multidimensional Inventory of Development, Sex, and Aggression (MIDSA)			✓			Youth emotional denial and intimacy	✓	✓	✓	✓
The Inventory of Parent and Peer Attachment - Revised (IPPA-R)			✓			Youth parental attachment style	✓	✓	✓	✓
Child Attachment Interview (CAI)				✓		Youth attachment	✓		✓	
Loeber Caregiver Questionnaire (LCQ)	✓		✓			Quality of parenting	✓	✓	✓	✓
Family Adaptability and Cohesion Scales (FACES-IV)	✓					General family function	✓	✓	✓	✓
Child and Adolescent Service Use Schedule (CA-SUS)		✓		✓		Service use (economics)	✓	✓	✓	✓
Conflict Tactics Scales (CTS)	✓					Parental disruption	✓	✓	✓	✓
General Health Questionnaire-28 (GHQ-28)	✓					Parent mental health	✓	✓	✓	✓
EQ-5D			✓			Youth measure of health outcome	✓	✓	✓	✓
Children and Young People - Resources, Evaluation and system Schedule (CYPRESS)					✓	Service context				✓
Qualitative interview		✓		✓		Youth and parental experience of multisystemic therapy for youth with problem sexual behaviours (MST-PSB)		✓		

### Statistical analysis plan

All analysis will be according to the intention-to-treat principle. The characteristics of the treatment groups will be described at baseline. Preliminary analysis will investigate the pattern of missing follow-up data.

### Primary outcome

The primary outcome of the proportion of cases where a sexual offence has been incurred during the follow-up period will be described by a Kaplan-Meier graph and summarized by the proportions in each group with a new sexual offence by 20 months. The linked outcome of out-of-home placement will also be described by a Kaplan-Meier graph and summarized by the proportions in each group with out-of-home placement by 20 months. The number of events will be estimated in order to inform power calculations for a fully powered efficacy trial.

For time-to-event offending outcomes, the event rate will be estimated. For continuous secondary outcomes, such as questionnaire data, linear mixed effects models will be fitted in order to estimate the individual-level residual variance.

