**Methods/Design:**

Eighty participants and their families recruited from five London boroughs will be randomized to MST-PSB or management as usual with follow-up to 20 months post-randomization. The primary outcome is out-of-home placement at 20 months. Secondary outcomes include sexual and non-sexual offending rates and antisocial behaviours, participant well-being, educational outcomes and total service and criminal justice sector costs. Feasibility outcomes include mapping the clinical service pathways needed to recruit adolescents displaying problematic sexual behaviour, acceptability of a randomized controlled trial to the key systems involved in managing these adolescents, and acceptability of the research protocol to young people and their families. Data will be gathered from police computer records, the National Pupil Database and interviews and self-report measures administered to adolescents and parents and will be analysed on an intention-to-treat basis.

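### The primary offence summary does not carry out the protocol's own rule that placed or incarcerated participants are not counted as non-offenders

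*Protocol article*

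**What the plan says.** The Primary outcomes section defines the primary outcome as "the proportion of documented cases of offending within 20 months of randomization", and names long-term out-of-home placement as a linked outcome. It then joins the two with a classification rule. The rule covers "all participants who are placed into local authority care, are incarcerated, long-term hospitalized or offered residential schooling". Anyone to whom this happens "at any time in the 20 months following randomization will not be considered to have moved from the offending to the non-offending group". Under that rule a participant is a non-offender at 20 months only if free of both a documented offence and a qualifying placement.

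The Primary outcome paragraph of the Statistical analysis plan section works differently. There, the share of cases "where a sexual offence has been incurred during the follow-up period will be described by a Kaplan-Meier graph". The same outcome is to be "summarized by the proportions in each group with a new sexual offence by 20 months". Placement is handled on its own: "The linked outcome of out-of-home placement will also be described by a Kaplan-Meier graph", again with proportions at 20 months. The same paragraph says that the numbers of events will feed the power calculation for a full efficacy trial.

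Two other places bear on this. The sample-size section defines non-offender status by absence of an arrest leading to conviction and does not mention placement. The abstract says "The primary outcome is out-of-home placement at 20 months".

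**The concern.** The rule in the Primary outcomes section recognises that someone removed from the community has not shown that they stopped offending. The analysis section fixes a summary that drops this: a young person placed early who has no new sexual offence adds to the denominator and not to the numerator.

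Unequal placement between arms is foreseeable from the document. All participants are recruited because they are at high risk of placement, MST-PSB is meant to reduce placement, and some of the listed MAU options are residential. Two things are then at stake. The offence-only comparison may shift against the arm that keeps more young people at home. And the event proportion carried into the design of a full trial depends heavily on which section is followed.

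**Working it through.** The plan gives no figure to reproduce on this point. Its sample size of 56 does not enter.

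**Step 1: the two rules side by side.**

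| Participant by 20 months | Primary outcomes section | Analysis section, offence proportion |
|---|---|---|
| New sexual offence | offender | event |
| No offence, qualifying placement | not a non-offender | non-event |
| No offence, no placement | non-offender | non-event |

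The sections disagree in the middle row. That needs no assumption about rates.

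**Step 2: inputs for the size.**
- Community risk of a sexual offence over 20 months, p = 14% in both arms. This is the top of the 5 to 14% sexual reconviction range in the Background. Applying it to 20 months is an assumption.
- Placed by 20 months: 30% MAU, 10% MST-PSB. Assumed; the document gives no placement rates.
- Placement starts at a uniform time in months 0–8 and lasts to month 20. Assumed.
- No recorded sexual offending while placed. Assumed, then relaxed.

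**Step 3: offence-only proportion.** The monthly hazard is h = −ln(0.86)/20 = 0.00754, so 8h = 0.0603. For a placed participant, the chance of an offence before placement is r = 1 − (1 − e^(−8h))/(8h) = 0.0296. The arm proportion is (1 − q)p + qr, where q is the proportion placed.
- MAU: 0.7 × 0.14 + 0.3 × 0.0296 = 10.7%
- MST-PSB: 0.9 × 0.14 + 0.1 × 0.0296 = 12.9%
- Gap: 2.2 points, or 0.022 × 40 = 0.9 of a participant per arm of 40

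**Step 4: sensitivity.** The gap is (0.30 − 0.10) × (p − r), with r now the 20-month risk of a placed participant.

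| Offence hazard while placed, relative to home | Gap at p = 14% | Gap at p = 5% |
|---|---|---|
| 0 | 2.2 points | 0.8 points |
| 0.5 | 1.1 points | 0.4 points |
| 1 | 0 | 0 |

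A second model, with constant hazards and 20% versus 60% placed by 20 months (also assumed), gives the same direction at p = 14% with full suppression: 12.6% in the arm with fewer placements against 9.3% in the other.

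**Step 5: the placement rule on the Step 2 inputs.** To isolate the effect of the rule, the offence component is kept as sexual offences. The proportion with an offence or a placement is q + (1 − q)p.
- MAU: 0.30 + 0.7 × 0.14 = 39.8%
- MST-PSB: 0.10 + 0.9 × 0.14 = 22.6%

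The direction reverses, and the event proportion rises from about 11–13% to about 23–40%. In the second model, 12.6% and 9.3% become 31% and 66%.

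**Step 6: can the two planned results be combined to give this?** No. Knowing only 10.7% with an offence and 30% placed in MAU, the composite could lie anywhere from 30.0% (everyone with an offence was also placed) to 40.7% (no overlap). It is 39.8% here because the overlap is 0.3 × 0.0296 = 0.9%. The joint status is needed, and neither graph shows it.

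**The case against.** The strongest reply is that the proportion with a recorded sexual offence by 20 months, whatever else happens, is a legitimate intention-to-treat quantity. Fewer offences because young people are placed is then part of what MAU does. The article says recorded offending is what funders care about, and it reports placement alongside. The section is descriptive and states no between-arm test. A 2-point gap is small against a standard error of about √(2 × 0.12 × 0.88/40) = 7 points.

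Much of this stands. The offence-only proportion is worth keeping, and the gap would be hard to see in 80 participants. But the objection does not explain why the classification rule disappears, and it does not touch the effect on the next trial's power calculation.

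A reader might go further and infer that the Kaplan-Meier curve keeps placed participants at risk as offence-free and so biases the trial against MST-PSB. The document does not support that. It does not say how the risk set is handled, and that detail may sit in an analysis plan not shown. Nor does it say that offending or its recording stops in local authority care or residential school. A young person placed after a new sexual offence is already an event and adds nothing to the gap.

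There is also a fair objection to replacing the offence outcome with the composite. In Step 5 the composite differs by 17.2 points with identical community offending, and residential MAU programmes could count as failures.

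**Conclusion.** The inconsistency is established from the text alone: the primary summary in the analysis section does not implement the rule in the Primary outcomes section, and the two separate curves cannot recover it.

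The distortion of the offence-only comparison is conditional. It needs unequal placement and less recorded offending during placement. It is about 2 points under the stated assumptions at the top of the cited risk range, smaller at lower risk or partial suppression, and zero with no suppression. The document supports the words can disadvantage, not does bias.

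The firmer practical consequence is for the full trial's design, where the choice of rule moves the event proportion from about 11–13% to about 23–40% on these inputs. It is worth correcting but does not undermine the feasibility trial.

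**What to change.** In the Primary outcome paragraph of the analysis section:

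1. Add the status from the Primary outcomes section, a documented offence or qualifying placement by 20 months, as a Kaplan-Meier outcome (time to whichever comes first) and as a proportion per arm.
2. Report it beside the offence-only and placement-only results, not in place of them. Show its components by which came first, so that a placement difference is not read as an offending difference.
3. Where placement dates allow, also give the offence rate per month in the community.
4. Say which event proportion will be used to plan the full trial.

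The edit should also settle which outcome is primary, since the abstract names placement, the Primary outcomes section documented offending, and the analysis section sexual offences.

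The cost is a change of wording and a little more analysis. The planned placement graph already needs placement start dates, and police records are collected "including details of custodial sentences". End dates of non-custodial placements are not mentioned, so item 3 depends on their being available. The drawback is that placement, including residential MAU options, may drive the composite, so its components must always be shown.
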